## Abstract

**Background:**

Acute respiratory failure, a major cause of death in COVID-19, is managed with high-flow oxygen therapy via invasive mechanical ventilation. In resource-limited settings like Nigeria, the shortage of ventilators and oxygen supply makes this option challenging. Evidence-based non-invasive alternatives to mechanical ventilation such as the use of continuous positive airway pressure (CPAP) devices exist, but there have been concerns that non-invasive ventilation may expose healthcare workers to infection from aerosolized dispersion of SARS-CoV-2. We propose to evaluate the feasibility, adaptability and acceptability of a CPAP/O_2_ helmet solution for non-invasive ventilation among patients with COVID-19 and health workers in eight COVID-19 treatment and isolation centers in Nigeria.

**Methods:**

The study will occur in 4 stages: (1) convene a Steering Committee of key stakeholders and recruit implementation sites; (2) use the integrated Promoting Action on Research Implementation in Health Services (i-PARiHS) framework to guide a needs assessment of treatment centers’ capacity to use high-flow oxygen therapy to treat COVID-19 patients and utilize the findings to develop an implementation strategy for the use of a CPAP/O_2_ helmet solution; (3) build infrastructure to support training and data monitoring processes and to develop implementation protocols to evaluate the adaptability of the strategy for the use of the CPAP/O_2_ helmet; and (4) train health workers, distribute a CPAP/O_2_ helmet solution for non-invasive ventilation, pilot test the implementation strategy, and assess feasibility of its use and acceptability that includes monitoring altered risk of SARS-CoV-2 infection among healthcare workers.

**Discussion:**

The CPAP/O_2_ helmet solution for non-invasive ventilation in Nigeria can serve as a scalable model for resource-poor countries, and beyond the COVID-19 pandemic, has the potential to be deployed for the treatment of pneumonia and other respiratory diseases.

**Trial registration:**

NCT04929691. Registered June 18, 2021—retrospectively registered, https://clinicaltrials.gov/ct2/show/NCT04929691

Contributions to the literature
Acute respiratory failure is a major cause of death in severe coronavirus disease 2019 (COVID-19).Evidence-based non-invasive alternatives to mechanical ventilation are needed to manage this condition.This paper describes a protocol to evaluate the feasibility, adaptability, and acceptability of a CPAP/O_2_ helmet solution for non-invasive ventilation among patients with COVID-19 and health workers in COVID-19 treatment centers in Nigeria.

## Background

The coronavirus disease 2019 (COVID-19) pandemic continues to surge across the globe, with more than 175 million persons infected with SARS-CoV-2 and causing over 2.6 million deaths, mostly due to acute respiratory failure [1]. With more than 89,000 deaths across sub-Saharan Africa, evidence-based just-in-time strategies that address acute shortage of ventilators and oxygen supply are in dire need, especially in countries like Nigeria, which accounts for over 20% of Africa’s population. Fortunately, the use of continuous positive airway pressure (CPAP) devices for non-invasive ventilation is an evidence-based alternative to mechanical ventilation [2–5]. CPAP and bilevel positive airway pressure (BiPAP) devices have been used in the management of patients with COVID-19 [6] and have inherent advantages, especially when intensive care resources are unavailable. CPAP and BiPAP machines can maintain positive end-expiratory pressure (PEEP) at 25 cmH_2_O and up to 50 l/min for FiO_2_ up to 95% with an appropriate patient circuit using supplemental oxygen flow [7]. When used with an oxygen helmet (O_2_ helmet), non-invasive ventilation (i) protects the treatment environment and healthcare workers from dispersion of the virus, (ii) improves outcomes [8], and (iii) reduces the need for mechanical ventilation [9]. CPAP devices can also run on 12 V DC, making them adaptable to battery use with solar-charging capability, an important consideration for low-income countries. CPAP devices are affordable, costing about 300 USD (1% the cost of a mechanical ventilator) and can readily be sourced from the approximately 3 million devices that are unused in U.S. homes to circumvent supply chain limits.

While randomized clinical trials have demonstrated the effectiveness of non-invasive ventilation (NIV) with BiPAP/O_2_ helmet use over face masks in reducing the need for endotracheal ventilation treatment of ARDS [10], CPAP/O_2_ helmet use has not been evaluated in low-resource settings like Nigeria, where mechanical ventilation is in limited supply, and oxygen as well as continuous electrical power supply is erratic. In response to this need, we established the CircumVent Project (www.circumventproject.com), a group of engineers, scientists, and clinicians, to develop a strategy to reduce the need for invasive mechanical ventilation and provide cost-effective alternative approaches for NIV in low- and middle-income countries (LMICs). The CircumVent Project will evaluate the feasibility of the CPAP/ O_2_ helmet solution using an implementation research framework that permits the exploration of the environment, the policy gaps, and the practice capacity for this non-invasive ventilation option in Nigeria. In this article, we describe the CircumVent Project as a potentially scalable model that can be implemented for large-scale deployment of CPAP/O_2_ helmets for non-invasive ventilation in Nigeria and other LMICs.

## Methods

### Study setting

The study will be conducted in eight COVID-19 treatment and isolation centers in Nigeria. The sites were selected based on availability of COVID-19 treatment services, geographic spread and patient volume. The eight sites are as follows: Aminu Kano Teaching Hospital; Delta State University Teaching Hospital; Federal Medical Centre, Abeokuta; Federal Medical Centre, Ebute Metta, Lagos; Lagos University Teaching Hospital; University College Hospital, Ibadan; University of Nigeria Teaching Hospital; and Alex Ekwueme Federal University Teaching Hospital.

### Study aims

1: Convene a Steering Committee of key stakeholders and recruit implementation sites to provide oversight for the development of processes for communication, decision-making, coordination, and distribution of CPAP/O_2_ helmet solutions for non-invasive ventilation at the eight COVID-19 treatment and isolation centers.

2: Use the integrated Promoting Action on Research Implementation in Health Services (i-PARiHS) framework to guide needs assessment, perform stakeholder analysis of the treatment centers’ capacity to use high-flow oxygen therapy to treat COVID-19 patients, and use the findings to develop a context-specific, practice facilitation strategy to implement the CPAP/O_2_ helmet solution for non-invasive ventilation.

3: Build infrastructure to support training and data monitoring processes and develop implementation protocols to evaluate the adaptability of the strategy for implementing use of CPAP/O_2_ helmets for non-invasive ventilation.

4: (a) Train healthcare workers; distribute a CPAP/O_2_ helmet solution for non-invasive ventilation, pilot test the practice facilitation [implementation] strategy, and assess feasibility of its use and acceptability; (b) estimate the altered risk of SARS-CoV-2 infection among healthcare workers associated with the use of CPAP/O_2_ helmets for non-invasive ventilation.

### Study design

The study will be performed in four phases: (1) assessment of the implementation climate (supply chain, distribution capacity, training); (2) deployment of CPAP/O_2_ helmet kits to each of the eight COVID-19 treatment centers in Nigeria and Training-of-Trainers (physicians) on the use of the CPAP/O_2_ helmet for the management of acute respiratory distress. The trainers will subsequently train non-physician personnel at their facilities on the use of the equipment; (3) assessment of acceptability of the CPAP/O_2_ helmets by physicians involved in the management of COVID-19 patients, and (4) assessment of change in the prevalence of COVID-19 infection among health care workers due to use of CPAP/O_2_ helmets for respiratory therapy.

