### Is the use of the CPAP/oxygen helmet associated with a greater risk of COVID-19 infection among healthcare workers? (specific aim 4 b)

Healthcare personnel are at increased risk of acquiring COVID-19 infection [18]. Studies of other respiratory pathogens have documented increased transmission risk associated with aerosol generating procedures (AGP), many of which can generate both large droplets and small particle aerosols. Non-invasive ventilation is considered an AGP, but it is postulated that helmet ventilation may be associated with less risk of transmission of respiratory pathogens via aerosolization given containment in the helmet and negligible air dispersion.

A case-control study design will be implemented. We will enroll clinical and environmental hospital staff who have exposure to SARS-CoV-2 via provision of direct patient care or environmental care at the eight CircumVent study sites. Consenting and eligible health care workers will complete baseline testing for SARS-CoV-2-specific antibodies and complete an exposure assessment form summarizing risk factors and potential COVID-19 exposures in the prior 1 month. All healthcare workers assessed at time 0 comprise the retrospective study cohort. Individuals who test negative for COVID-19 antibodies at time 0 will be invited to participate in the prospective study. They will be followed for up to 6 months during which they will complete monthly encounter forms to assess community and healthcare-related exposures and to document any PCR-confirmed diagnoses of SARS-CoV-2 infection. However, the study will be censored and exit interview and a second sample for SARS-CoV-2 antibodies will be obtained if and when COVID-19 vaccine becomes available at the designated COVID-19 treatment centers.

In the retrospective study, a case is defined by seropositivity to SARS-CoV-2-specific antibodies, and a control is defined by seronegativity to SARS-CoV-2-specific antibodies. In the prospective study, a case is defined by seropositivity to SARS-CoV-2-specific antibodies, or a clinical case of SARS-CoV-2 infection confirmed by PCR testing, and a control is defined by the absence of infection, either by SARS-CoV-2 PCR or SARS-CoV2 specific antibodies.

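### Study design phase 4 promises a change in infection prevalence caused by helmets, which the design described for aim 4b (labelled case-control, in fact a serosurvey plus a cohort) cannot estimate

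*Protocol article*

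**What the plan says.** The protocol article states the healthcare-worker infection objective in two ways.

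- Study design, phase 4: "assessment of change in the prevalence of COVID-19 infection among health care workers due to use of" CPAP/O2 helmets. This is a change over time or between conditions, attributed to the helmet.
- Study aims, 4(b): "estimate the altered risk of SARS-CoV-2 infection among healthcare workers associated with the use of" the helmets. This is an association with risk. The heading of the specific aim 4 b section is also worded as an association.

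The specific aim 4 b section then describes the design:

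- Label: "A case-control study design will be implemented".
- Measurement at time 0: consenting staff "will complete baseline testing for SARS-CoV-2-specific antibodies and complete an exposure assessment form".
- Look-back of that form: it is described as "summarizing risk factors and potential COVID-19 exposures in the prior 1 month".
- Who is kept: "All healthcare workers assessed at time 0 comprise the retrospective study cohort". Cases are the seropositive and controls the seronegative.
- Who is followed: "Individuals who test negative for COVID-19 antibodies at time 0 will be invited to participate in the prospective study".
- Length of follow-up: "They will be followed for up to 6 months", or for less time if a vaccine reaches the centers.

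Quantitative data analysis compares exposures between cases and controls with chi-square or Fisher's exact tests. Variables that pass at P < 0.05 go into a forward logistic regression, whose output is described only in general terms as association measures.

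**The concern.** A change in prevalence *due to* helmets is a causal claim about two prevalences. The design supplies one prevalence, at time 0, and then the occurrence of new infection in those who were negative. If phase 4 stands as written, the report may offer a causal safety statement that the data cannot carry. Infection of healthcare workers by aerosol is the worry that the article's Abstract raises about non-invasive ventilation, and the Discussion presents the findings as pilot data for scale-up elsewhere.

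The case-control label adds to the problem. It points the analysis towards comparing exposures by outcome status, as if risks were out of reach, when the enrolment described makes them directly available. Aim 4b asks about risk.

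**Working it through.** The article gives no sample size, effect size or infection level for aim 4b, so there is no figure of its own to reproduce. The check sets the sections against each other and then sizes the effect-measure issue under stated assumptions.

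**1. Could a change in prevalence due to helmets be estimated?**

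- *Between sites:* no. Study design sends kits to all eight centers, and aim 4b enrols staff at the same eight.
- *Over time:* no second prevalence is planned. Follow-up is restricted to baseline seronegatives, so it measures new infection. A later cumulative prevalence could be pieced together as p + (1 − p) × i, where p is prevalence at time 0 and i is the proportion of seronegatives newly infected. With assumed p = 20% and i = 10%, this is 0.20 + 0.80 × 0.10 = 28%. With everyone once positive counted as infected, this quantity cannot fall. It would rise with the epidemic even if helmets protected.
- *Timing of time 0:* the text does not tie it to deployment. Study design lists deployment second and the infection assessment fourth. If time 0 follows deployment, there is no pre-helmet prevalence. If it precedes deployment, the one-month look-back cannot contain exposure to the study's helmets, so the retrospective part cannot address aim 4b. Neither order yields the phase 4 quantity.

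**2. Is it a case-control study?**

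Case-control sampling selects people by outcome. Here everyone assessed at time 0 is retained, every seronegative is invited to follow-up, and no case-to-control ratio is stated. The first part is a cross-sectional serosurvey and the second a cohort. Both have denominators. For example, assume 400 exposed and 400 unexposed workers:

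- 30% v 20% infected (120 and 80): prevalence ratio 0.30/0.20 = 1.50, difference +10 points, OR = (120 × 320)/(80 × 280) = 1.71.
- 10% v 20% infected (40 and 80): prevalence ratio 0.50, difference −10 points, OR = (40 × 320)/(80 × 360) = 0.44.

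**3. How far apart are odds ratio and risk ratio?**

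RR = OR / (1 − p0 + p0 × OR), where p0 is the risk in the unexposed. The p0 values are assumptions.

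| p0 | RR when OR = 2.0 |
|---|---|
| 2% | 2/1.02 = 1.96 |
| 5% | 2/1.05 = 1.90 |
| 10% | 2/1.10 = 1.82 |
| 20% | 2/1.20 = 1.67 |
| 40% | 2/1.40 = 1.43 |

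In the protective direction, a true RR of 0.5 gives an OR of 0.49 at p0 = 5%, 0.44 at 20% and 0.37 at 40%. Misreading moves the effect away from 1 in whichever direction it lies.

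**The case against.** The strongest reply is that phase 4 is one line in a summary list. Study aims and the aim 4b heading both use association wording, so phase 4 is the outlier and the working objective is already sound. It is true that phase 4 is the outlier. But it stands in the Study design section and is the only place where the objective is causal, so it needs correcting.

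Three stronger readings are tempting, and the document does not support them.

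- *There is no before-helmet measure.* There is an antibody test at time 0. What the text lacks is its timing relative to deployment and any planned before/after comparison. The timeline figure (Fig. 2), which might give the timing, was not available to this review.
- *Risk would be overstated.* The article gives no infection level and never says that an odds ratio will be read as a risk ratio. Odds ratios are the natural output of logistic regression, but the article does not name them. If misreading occurred, the direction would depend on the truth: with the reduced transmission that the aim 4b section postulates, protection would be exaggerated. At 2% to 5% baseline risk the gap is small.
- *With no helmet-free site, no contrast is possible.* Workers within a site can differ in helmet exposure, and exposure is recorded individually at baseline and monthly. An association can be estimated; a prevalence change caused by helmets cannot.

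It is also fair to say that a condensed article may leave the choice of regression model to the full plan. That limits the effect-measure point to a recommendation. It does not excuse a conflicting objective or a wrong design label, both of which are in print.

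**Conclusion.** The point holds. The phase 4 objective cannot be delivered by the design and analysis described, and it conflicts with aim 4b. The case-control label does not describe the enrolment, which is a serosurvey plus a cohort from which prevalence and risk can be estimated directly. These conclusions rest on the text alone.

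The size of the effect-measure issue is conditional on two things the article does not state: the infection level, and whether an odds ratio would be read as a risk ratio. If it were, the gap for an odds ratio of 2.0 runs from negligible at 2% baseline risk to substantial at 40%. This part is secondary and is no evidence that risk will be overstated.

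**What to change.** 1. Reword phase 4 to match aim 4b: estimate the association between helmet exposure and (a) prevalent infection at time 0 and (b) new infection among initially seronegative workers. Drop the change in prevalence and the causal wording.
2. Call the first part a cross-sectional serosurvey and the second a cohort.
3. State when time 0 falls relative to helmet deployment.
4. For helmet exposure, report the prevalence ratio and difference (serosurvey) and the risk ratio and difference (cohort), each with a 95% CI, beside any odds ratio. They can be standardised from the logistic model. Helmet exposure must then be in that model whether or not it passes the univariable screen.

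The cost is a more modest stated objective and slight extra analysis. No additional participants, visits or samples are needed.

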### Conceptual framework

We will evaluate the feasibility of a CPAP/O_2_ helmet solution for non-invasive ventilation using the i-PARiHS framework. The core constructs of the framework include *facilitation*, *innovation*, *recipients,* and *context*, with *implementation facilitation* as the active element that integrates the other constructs. i-PARiHS posits that successful implementation of a program is specified in terms of the achievement of its goals, which results from facilitation of an innovation with the recipients and their context (local, organizational and health system) in which the program is being implemented [11]. i-PARiHS will guide the planning of the proposed study in 4 steps: *practice capacity assessment*, *training*, *distribution*, and *user testing.* Because scale up of an evidence-based program requires expertise to facilitate multilevel system changes [12], and LMICs often lack such expertise, we will use i-PARiHS to explore factors and support systems required for the successful use of CPAP/O_2_ helmets for non-invasive ventilation at the eight COVID-19 treatment centers in Nigeria.

### Study procedures

#### Treatment protocol for the CPAP/O_2_ helmet system

The treatment protocol was designed in line with World Health Organization (WHO) and Nigerian national COVID-19 treatment guidelines. The patient interface is a low-cost Subsalve (North Kingstown, RI) oxygen helmet that can protect healthcare workers from viral exposure when used with disposable inspiratory and expiratory 22-mm viral filters (Fig. 1). The tubing and helmet can be sterilized in a variety of ways [13], including using low-cost steramine that is proven effective against SARS-CoV-2. The viral filters will prevent aerosolizing the SARS-CoV-2 virus and infecting healthcare providers for COVID-19 patients. Importantly, the oxygen helmet solves a problem that has contributed to the intubation of patients for mechanical ventilation, when NIV was also a feasible treatment [14–16].

**Fig. 1 Fig1:**
[figure not shown]
Patient circuit 1. Non-invasive positive pressure ventilation

#### Convening of Steering Committee (specific aim 1)

The membership of the Steering Committee will be drawn from the Presidential Task Force on COVID-19; the Nigeria Ministry of Health, Directors of the COVID-19 Treatment and Isolation Centers, and the Nigeria Centre for Disease Control (NCDC). The Steering Committee will (1) identify the capacity of the eight COVID-19 treatment centers to use the CPAP/O_2_ helmet solution for non-invasive ventilation through stakeholder engagement, and (2) develop a context-specific practice facilitation strategy for use of the CPAP/O_2_ helmet kits in local hospitals. The Steering Committee will meet every 3 months (Fig. 2).

**Fig. 2 Fig2:**
[figure not shown]
Timeline of project activities

#### Implementation Committee

The Implementation Committee is comprised of medical directors/representatives of five of the eight COVID-19 isolation and treatment centers in Nigeria. The committee oversees implementation of the project including (a) identifying practice capacity of all eight COVID-19 treatment centers, (b) establishing a manual of procedures and data collection processes, (c) finalizing plans for program evaluation, and (d) testing the feasibility and acceptability of using the CPAP/O_2_ helmet solutions for NIV in COVID-19 patients. The Implementation Committee has been meeting weekly since June 2020 and since January 2021, meeting monthly.

#### Needs assessment (specific aim 2)

The structured needs assessment will explore treatment procedures for management of acute respiratory failure at the COVID-19 treatment centers, document staffing, staff characteristics (professional designation, training, experience), workload, facility characteristics (infrastructure, relevant supplies, oxygen supply), and service organization. The Steering Committee will employ findings from the needs assessment to refine all metrics to reflect usability of the measures and maintain scientific rigor.

We will use qualitative interviews and domains of i-PARiHS, to understand the context, barriers, and facilitators of implementing the CPAP/O_2_ helmet solution for non-invasive ventilation and contextual features of the COVID-19 treatment centers that will enable its implementation. These interviews will explore the following: (1) evidence of the likely fit of the treatment centers for use of the CPAP/O_2_ helmet solution for non-invasive ventilation; (2) the recipients and key stakeholders likely to be involved with implementing the use of a CPAP/O_2_ helmet solution for non-invasive ventilation in management of acute respiratory failure in COVID-19 patients, with a focus on the barriers that may influence its implementation; (3) context, resources and leadership support likely to influence acceptability and adaptability of the CPAP/O2 helmet solution for non-invasive ventilation; and (4) facilitation and the factors likely to enable recipients’ acceptability of the CPAP/O_2_ helmet solution for non-invasive ventilation.

Data will be collected from 16 physicians attending the CircumVent training who were selected from the participating health facilities. An interview guide will be developed, piloted, and used for the interviews. Participants will be contacted to schedule a convenient time for their interviews. Semi-structured interviews will be conducted in the English language. The opened-ended questions will allow the participants to express their opinions and share their experiences in the use of the CircumVent equipment, and suggestfactors that could promote or inhibit the use of the equipment. Prompts will be used to encourage participants to provide insight. Each interview will be audio-recorded. Each qualitative interview will last about 45 min. These data will inform development of the context-specific practice facilitation strategy.

